| Data/ Statistical Analysis For all parts of the study, the population will be people with new-onset type 2 diabetes in CPRD from 2006 (see section K, above) and the exposure will be ethnicity (either South Asian vs. European [baseline] or African Caribbean vs. European [baseline], as detailed in section L, above). Covariates in base models will include age and sex, and further covariates will be considered individually, as outlined in section vi) below. Statistical analysis is further considered by objective:   1. **Outcome**: time to initiation of first-line anti-diabetic medication, probability of receiving anti-diabetic 1 year post-diagnosis   **Entry**: date of type 2 diabetes diagnosis  **Exit**: date of first anti-diabetic prescription (defined by the absence of a prescription for the medication in the previous 6 months’ records), or end of study/ leaving CPRD practice/ death  **Analysis**: summary statistics will be compared by ethnicity using Kaplan-Meier time-to-event analysis (cumulative failure probability in a given time frame by ethnicity, comparison of medians by log-rank test), Cox proportional hazards regression models will be used to adjust for confounding/ investigate potential mediators  **Example effect measure**: hazards ratio (HR) for anti-diabetic prescription   1. **Outcome:** proportions of patients prescribed medication from each anti-diabetic (stratified by first- to third-line treatment), antihypertensive and lipid-lowering class (defined by the absence of a prescription for the medication in the previous 6 months’ records)   **Sub-population:** a) all participants starting first- to third-line anti-diabetic treatment, b) all patients on antihypertensives, or c) all patients on lipid-lowering medication  **Analysis:** proportions receiving each drug will be compared by ethnicity, then logistic regression models will be used to adjust for confounding/ investigate potential mediators  **Example effect measures**: odds ratio (OR) of being prescribed metformin (=1) vs. non-metformin medication (=0) at first stage of treatment, OR of being prescribed sulphonylurea (=1) vs. non- sulphonylurea medication (=0) at second stage of treatment, OR of calcium-channel blocking antihypertensive prescription vs. non- calcium-channel blocking antihypertensive in those on antihypertensive treatment, OR of statin prescription vs. non-statin lipid-lowering medication prescription in those with >10% 10 year cardiovascular risk   1. **Outcome:** proportions of patients prescribed each dose of each anti-diabetic, antihypertensive and lipid-lowering medication, stratified by treatment stage (defined by the absence of a prescription for the medication in the previous 6 months’ records)   **Sub-population:** a) all participants on first- to third-line anti-diabetic treatment, b) all patients on antihypertensives, or c) all patients on lipid-lowering medication  **Analysis: :** proportions receiving each dose of each drug will be compared by ethnicity, then logistic regression models will be used to adjust for confounding/ investigate potential mediators  **Example effect measures**: OR of being prescribed maximum dose (2g daily) vs. sub-maximum dose of metformin, OR of being prescribed atorvastatin 10mg per day vs. higher doses (20mg, 40mg or 80mg)   1. **Outcome:** yearly monitoring rate post commencement of medication from each anti-diabetic (first- to third-line), antihypertensive and lipid-lowering class – i.e. number of times HbA1c/ blood pressure/ blood lipids measured per person-year of follow-up, stratified by year after commencement; may be multiple entry dates per person for different medications   **Entry:** first use of any medications of interest from 2006 onwards  **Exit:** first of; end of strata (e.g. 1 year after medication commencement), end of study/ leaving CPRD practice/ death  **Analysis:** summary statistics will be compared by ethnicity, Poisson regression modelling used to adjust for confounding/ investigate potential mediators  **Example effect measures**: yearly monitoring rate ratios (RRs)   1. **Outcome:** time to medication intensification (up-titration, addition or switching) after detection of sub-optimal control of diabetes, hypertension or blood lipids, or probability of intensification 1 year post-detection of sub-optimal control; may be multiple entry dates per person for different medications   **Entry:** date when sub-optimal risk factor control detected (see section M for how this is defined for each risk factor)  **Exit:** first of; date of anti-diabetic, antihypertensive or lipid-lowering treatment intensification, end of study/ leaving CPRD practice/ death  **Analysis:** summary statistics will be compared by ethnicity using Kaplan-Meier time-to-event analysis (cumulative failure probability in a given time frame by ethnicity, comparison by log-rank test), Cox proportional hazards regression models will be used to adjust for confounding/ investigate potential mediators  **Example effect measures**: cumulative failure probability for each ethnic group 1 year post detection of sub-optimal value, comparison of median survival times using the log-rank test by ethnicity, HRs of intensification stratified by year   1. **Outcome:** influence of deprivation, polypharmacy, multi-morbidity, drug adherence (iv) and v) only), patient engagement with healthcare, diabetes duration and HbA1c on any ethnic differences found in i) to v).   **Entry:** as above for i), iv) and v)  **Exit:** as above for i), iv) and v)  **Analysis:** as above for i) to v)  **Covariates:** smoking status, BMI, deprivation, polypharmacy, multi-morbidity, drug adherence, patient engagement with healthcare, diabetes duration and HbA1c  **Effect measures:** we will observe the degree of attenuation of the ethnic difference effect measure for each outcome when each covariate is inserted in turn to models, and thus evaluate the likelihood of confounding or mediation  Sub-group/ sensitivity analyses  Analyses will be stratified by age group, and changes in guidelines and temporal trends in drug usage will be accounted for by stratifying by time.  Three sensitivity analyses will be performed – all to boost ethnicity ascertainment. Firstly, on the 58% of CPRD participants with linked secondary care data from Hospital Episode Statistics (HES) (19), using ethnicity codes from HES - present in 78% (18). Secondly, on new registrants since 2006, 78% of whom have ethnicity codes recorded (19). Thirdly, on patients from practices in the London area; where previous research indicates ethnicity recording to be approaching 60% (28).  Plans for addressing misclassification and bias  ­Plans for addressing misclassification of diabetes status and ethnicity are given above (see sections K and L respectively).  Selection bias may arise in ethnicity recording, i.e. greater recording for patients from ethnic minorities, and may also vary across time (with greater recording after the introduction of incentives in 2004) and geographically (greater in urban areas with more ethnic diversity (28) than rural ones with less). We plan to address this in three ways, as detailed above under the “sub-group/ sensitivity analyses” heading. NB/ we do acknowledge these approaches may in themselves introduce bias, and thus we will carefully compare baseline characteristics between the sensitivity and primary analysis populations.  Though primary care prescription data are almost entirely computerised, bias may be introduced into the descriptive arms of the study from unrecorded prescriptions issued in secondary care; equally medication started in secondary care and continued in primary care may falsely lengthen times to up-titration. We anticipate little bias in the monitoring outcome, where blood tests and clinical data such as blood pressure (including those recorded in secondary care) are generally automatically entered into notes via specific templates. Additionally, some bias may be present regarding the ascertainment of treatment intensification, where the intervention is non-pharmacological or constitutes referral to another service. Therefore we will also search for codes indicating lifestyle modification advice or referral which are chronologically close to the medication exposure period.  We plan to examine the influence of drug adherence in explaining any associations between ethnicity and prescribing, but this will only be measured by proxy using the proportion of days covered method; we are unable to verify whether prescriptions have been obtained from pharmacies or whether medication has been taken.  Multiple comparisons  As the study will involve multiple comparisons, findings will be interpreted with caution, and attention paid to clinically meaningful effect sizes rather than p values per se. |

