| L. Definition of the Study population All permanently-registered patients with research-standard data and incident type 2 diabetes Read codes from at least 1 year after 1^st^ January 2006 (start of follow-up; coinciding with when ethnicity was recorded for ≈80% of new registrations (17)) to 31^st^ December 2018 in the CPRD. The study will be restricted to incident cases to enable more precise measurement of treatment stage; people with prevalent type 2 diabetes Read codes prior to 2006 will be excluded.  Type 2 diabetes will be defined by a previously tested algorithm that uses Read codes, medication, blood test results and diabetes-specific process of care Read codes to adjudicate diabetes status (27) – see appendix. Specific exclusions will include: type 1 diabetes, gestational diabetes, non-specified diabetes diagnosed at ≤40 years in Europeans or ≤35 years in South Asians and African Caribbeans (reducing misclassified type 1 diabetes), and secondary diabetes (e.g. drug-induced).  In people without diabetes, those eligible for antihypertensive treatment will include people ≥40 years of age with incident: Read codes for hypertension, clinic BP of ≥160/100, ambulatory BP of ≥150/95 or clinic BP of ≥140/90 or ambulatory BP of ≥135/85 **plus either** 10 year CVD risk score exceeding 20% or 10% (for calendar years 2006-2013 and 2014-2019 respectively) **or** evidence of target organ disease (i.e. Read codes for left ventricular hypertrophy, chronic kidney disease, micro/ macroalbuminuria, or hypertensive retinopathy) (24). Those eligible for lipid-lowering medication will include people ≥40 years of age with an incident recording of CVD risk score ≥20% (if recorded between 2006 and 2013), or ≥10% (if recorded between 2014 and 2019), to account for guidelines changes (26)) during the study period. |

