| N. Exposures, outcomes and covariates *Data sources are listed in square parentheses*  Exposures:  For all objectives, the exposure is either South Asian or African Caribbean ethnicity (defined as above), with European ethnicity as the baseline category. *[Primary care clinical records]*  Health Outcomes by study objective:   1. Proportion of those eligible for primary prevention who are prescribed a) antihypertensives and b) lipid-lowering medication *[Primary care clinical records, prescription drug files]* 2. Time to first anti-diabetic/ antihypertensive/ lipid-lowering medication prescription. *[Primary care clinical records, prescription drug files.]* 3. Choice of a) anti-diabetic (first- to third-line), b) antihypertensive and c) lipid-lowering medications, see appendix for code lists for each (derived from chapters of the British National Formulary). *[Prescription drug files.]* 4. Doses used for each a) anti-diabetic, b) antihypertensive and c) lipid-lowering medication. *[Prescription drug files.]* 5. Monitoring rate, stratified by the time since treatment initiation, e.g. the number of a) HbA1c, b) BP or c) lipid measures divided by the amount of person time, within strata of time since initiation (i.e. first year, second year since initiation etc). *[Prescription drug files, test records.]* 6. Time to treatment intensification after detection of sub-optimal risk factor control. *[Primary care clinical records, prescription drug files, test records.]* Sub-optimal control will be classified as follows:    1. Diabetes; HbA1c≥53mmol/mol (7.5%) (7)    2. Hypertension; blood pressure≥140/80 mmHg, or 130/80 mmHg in those with neuropathy/ nephropathy or retinopathy (24)    3. Lipids; <40% reduction in non-HDL cholesterol (25) 7. Influence of the following on associations between ethnicity and prescribing: smoking, BMI, deprivation, polypharmacy, multi-morbidity, drug adherence (for outcomes iv) and v)), patient engagement with healthcare, diabetes duration and HbA1c. *[Linked IMD data, primary care clinical records, prescription drug files, test records.]*   Covariates (all taken from last entry in medical notes prior to follow-up time commencing)  Age *[Primary care clinical records]*  Sex *[Primary care clinical records]*  Smoking status *[Primary care clinical records]*  BMI *[Primary care clinical records]*  Deprivation (using patient-level IMD scores, with sensitivity analyses using practice-level IMD scores) *[Primary care clinical records, linked deprivation data]*  Polypharmacy (number of medications) *[Prescription drug files]*  Multimorbidity (defined by presence or absence of the following key co-morbidities: coronary heart disease, cerebrovascular disease, heart failure, atrial fibrilliation, hypertension, chronic kidney disease, peripheral arterial disease, retinopathy, neuropathy, cancer [any], COPD/ asthma, severe mental illness) *[Primary care clinical records]*  Patient engagement/ access (using the number of consultations in the year preceding diabetes diagnosis as a proxy) *[Primary care clinical records]*  Patient adherence (using the proportion of days covered: PDC=days of medication supplied per x day period/ x (27)). This will be calculated separately for all medications issued over the follow-up time of interest, and then a mean PDC for all medications will be derived for each patient. Both measures are important as adherence may vary by drug. *[Prescription drug files]*  Disease parameters: baseline HbA1c/ blood pressure and number of years since diabetes diagnosis *[Primary care clinical records, test records.]* |

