| O. Data/ Statistical Analysis For all parts of the study, the population will be people with and without new-onset type 2 diabetes active in CPRD from 2006 (see section K, above) and the exposure will be ethnicity (either South Asian vs. European [baseline] or African Caribbean vs. European [baseline], as detailed in section L, above). Covariates in base models will include age and sex, and further covariates will be considered individually, as outlined in section vi) below. Statistical analysis is further considered by objective:   1. **Outcome:** Proportion of those eligible for primary prevention who are prescribed a) antihypertensives and b) lipid-lowering medication   **Entry:** Date of incident a) hypertension Read code/ raised BP reading or b) elevated 10 year CVD risk score, at least 12 months after study start date of 1^st^ January 2005  **Exit:** First of; date of first antihypertensive/ lipid-lowering medication prescription (defined by the absence of a prescription for the medication in the previous 6 months’ records), end of study, leaving CPRD practice or death  **Analysis:** Proportions receiving antihypertensives/ statin will be compared by ethnicity, then logistic regression models will be used to adjust for confounding/ investigate potential mediators  **Example effect measure:** Odds ratio (OR) of receiving an antihypertensive/ lipid-lowering medication vs. not for each ethnic group of interest, stratified by time period since identification of hypertension/ elevated CVD risk   1. **Outcome**: time to initiation of first-line anti-diabetic/ antihypertensive/ statin, probability of receiving anti-diabetic/ antihypertensive/ statin at one year post-diagnosis/ identification of high CVD risk   **Entry**: date of type 2 diabetes diagnosis/ incident hypertension Read code or raised BP reading/ incident high 10 year CVD risk score recording  **Exit**: date of first anti-diabetic/ antihypertensive/ statin prescription (defined by the absence of a prescription for the medication in the previous 6 months’ records), or end of study/ leaving CPRD practice/ death  **Analysis**: summary statistics will be compared by ethnicity using Kaplan-Meier time-to-event analysis (cumulative failure probability in a given time frame by ethnicity, comparison of medians by log-rank test), Cox proportional hazards regression models will be used to adjust for confounding/ investigate potential mediators  **Example effect measure**: hazards ratio (HR) for anti-diabetic/ antihypertensive/ statin prescription   1. **Outcome:** proportions of patients prescribed medication from each anti-diabetic (stratified by first- to third-line treatment), antihypertensive and lipid-lowering class (defined by the absence of a prescription for the medication in the previous 6 months’ records)   **Sub-population:** a) all participants starting first- to third-line anti-diabetic treatment, b) all patients on antihypertensives, or c) all patients on lipid-lowering medication  **Analysis:** proportions receiving each drug will be compared by ethnicity, then logistic regression models will be used to adjust for confounding/ investigate potential mediators  **Example effect measures**: odds ratio (OR) of being prescribed metformin (=1) vs. non-metformin medication (=0) at first stage of treatment, OR of being prescribed sulphonylurea (=1) vs. non- sulphonylurea medication (=0) at second stage of treatment, OR of calcium-channel blocking antihypertensive prescription vs. non- calcium-channel blocking antihypertensive in those on antihypertensive treatment, OR of statin prescription vs. non-statin lipid-lowering medication prescription in those with >10% 10 year cardiovascular risk   1. **Outcome:** proportions of patients prescribed each dose of each anti-diabetic, antihypertensive and lipid-lowering medication, stratified by treatment stage (defined by the absence of a prescription for the medication in the previous 6 months’ records)   **Sub-population:** a) all participants on first- to third-line anti-diabetic treatment, b) all patients on antihypertensives, or c) all patients on lipid-lowering medication  **Analysis: :** proportions receiving each dose of each drug will be compared by ethnicity, then logistic regression models will be used to adjust for confounding/ investigate potential mediators  **Example effect measures**: OR of being prescribed maximum dose (2g daily) vs. sub-maximum dose of metformin, OR of being prescribed atorvastatin 10mg per day vs. higher doses (20mg, 40mg or 80mg)   1. **Outcome:** yearly monitoring rate post commencement of medication from each anti-diabetic (first- to third-line), antihypertensive and lipid-lowering class – i.e. number of times HbA1c/ blood pressure/ blood lipids measured per person-year of follow-up, stratified by year after commencement; may be multiple entry dates per person for different medications   **Entry:** first use of any medications of interest from 2006 onwards  **Exit:** first of; end of strata (e.g. 1 year after medication commencement), end of study/ leaving CPRD practice/ death  **Analysis:** summary statistics will be compared by ethnicity, Poisson regression modelling used to adjust for confounding/ investigate potential mediators  **Example effect measures**: yearly monitoring rate ratios (RRs)   1. **Outcome:** time to medication intensification (up-titration, addition or switching) after detection of sub-optimal control of diabetes, hypertension or blood lipids, or probability of intensification 1 year post-detection of sub-optimal control; may be multiple entry dates per person for different medications   **Entry:** date when sub-optimal risk factor control detected (see section M for how this is defined for each risk factor)  **Exit:** first of; date of anti-diabetic, antihypertensive or lipid-lowering treatment intensification, end of study/ leaving CPRD practice/ death  **Analysis:** summary statistics will be compared by ethnicity using Kaplan-Meier time-to-event analysis (cumulative failure probability in a given time frame by ethnicity, comparison by log-rank test), Cox proportional hazards regression models will be used to adjust for confounding/ investigate potential mediators  **Example effect measures**: cumulative failure probability for each ethnic group 1 year post detection of sub-optimal value, comparison of median survival times using the log-rank test by ethnicity, HRs of intensification stratified by year   1. **Outcome:** influence of deprivation, polypharmacy, multi-morbidity, drug adherence (iv) and v) only), patient engagement with healthcare, diabetes duration and HbA1c on any ethnic differences found in i) to v).   **Entry:** as above for i), iv) and v)  **Exit:** as above for i), iv) and v)  **Analysis:** as above for i) to v)  **Covariates:** smoking status, BMI, deprivation, polypharmacy, multi-morbidity, drug adherence, patient engagement with healthcare, diabetes duration and HbA1c  **Effect measures:** we will observe the degree of attenuation of the ethnic difference effect measure for each outcome when each covariate is inserted in turn to models, and thus evaluate the likelihood of confounding or mediation  Sub-group/ sensitivity analyses  See section O of original application  Plans for addressing misclassification and bias  See section O of original application  Multiple comparisons  See section O of original application |

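### Incident cases are defined from fixed calendar dates with no minimum registered time, so people who join a practice with existing treated disease can be counted as new cases

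*Supplement*

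**What the plan says.** The current text is the December 2019 amendment, together with the original sections that it keeps by reference.

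- **Diabetes (amended section L).** The cohort takes "incident type 2 diabetes Read codes from at least 1 year after 1^st^ January 2006 (start of follow-up", and "people with prevalent type 2 diabetes Read codes prior to 2006 will be excluded". The stated purpose is "The study will be restricted to incident cases to enable more precise measurement of treatment stage".
- **Registration (section L).** The population is "All permanently-registered patients with research-standard data". That sets a registration status and a data standard. It sets no length of registration before the first code.
- **Hypertension and high CVD risk (section O, objective i, Entry).** The qualifying entry must fall "at least 12 months after study start date of" 1 January 2005. This is again a calendar anchor.
- **First prescription (section O, Exit under objectives i and ii).** It is defined by the "absence of a prescription for the medication in the previous 6 months" of records. No rule says that six months of records must exist.
- **Engagement covariate (section N).** It is measured "using the number of consultations in the year preceding diabetes diagnosis as a proxy". No rule says that the patient must have been registered for that year.
- **Sensitivity analyses (original application, kept by reference).** The second is described as: "Secondly, on new registrants since 2006, 78% of whom have ethnicity codes recorded".

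**The concern.** Take a patient who registers with a new practice in 2012 with long-standing, treated hypertension. The new practice may enter its first hypertension code that year. The entry falls after the calendar anchor, there are no earlier prescriptions at that practice, and the patient qualifies as incident. The first repeat prescription then looks like initiation shortly after diagnosis, and a drug or dose from a later treatment stage can be recorded as first-line.

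This works against the stated purpose of the incident restriction, and it bears on the outcomes for initiation, time to first prescription, choice and dose. It also affects the missing-data argument. The plan defends complete-case analysis partly by adjusting for consultations in the year before diagnosis, and a recent joiner has only part of that year observed.

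The complete-case sample is also likely to over-represent joiners. Section L puts ethnicity recording at about 80% of new registrations, and the feasibility section puts it at about 50% of active patients.

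**Working it through.** **Step 1: look for a rule tied to the patient's own registration.** Amended sections L, N and O and the retained bias and missing-data sections contain none. Two patient-level checks exist:

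- The 6-month prescription-free rule identifies a first prescription, not incident disease. Someone who has just joined meets it automatically.
- The adjudication algorithm in section L uses codes, medication, test results and process-of-care codes to settle diabetes status. Its diagram is an appendix that is not shown. No counterpart is described for hypertension, raised blood pressure or CVD risk scores.

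The bias section covers ethnicity recording, secondary-care prescribing, non-drug intensification and adherence. It does not cover existing disease in new registrants.

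**Step 2: illustrate the possible size.** The plan's input is 42% with a first anti-diabetic prescription at one year (sample size section). All shares of already-treated joiners below are assumptions.

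Let f be the joiner share. A crude version lets joiners start at once:

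- One-year probability p = (1 − f) × 0.42 + f
- Crude HR = ln(1 − p_SA) / ln(1 − p_E)
- For 3% vs 5%: p = 0.4374 and 0.4490, and the HR is 1.036.

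That is not the Cox HR the plan will estimate, because immediate starters break proportional hazards. The Cox limit uses S(t) = (1 − f)·exp(−λt) + f·exp(−μt), where:

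- λ = −ln(0.58) = 0.545 per year, held constant (an assumption);
- μ = −ln(0.10) / (30/365) = 28.0 per year, so that 90% of joiners have a first recorded prescription within 30 days (an assumption).

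The log HR b solves ∫[w·d₁·(1 − π) − (1 − w)·d₀·π]dt = 0. Here π = w·S₁·e^b / (w·S₁·e^b + (1 − w)·S₀), d is the event density, and w = 10.5/130.9 = 0.080. The true HR is 1.00.

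| Assumed joiner share, Europeans vs South Asians | Crude ratio | Cox limit, 1 year | Cox limit, 5 years |
|---|---|---|---|
| 3% vs 5% | 1.036 | 1.05 | 1.02 |
| 3% vs 8% | 1.092 | 1.12 | 1.06 |
| 5% vs 10% | 1.091 | 1.12 | 1.06 |

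Using 70% within 30 days instead of 90% changes the Cox limits by less than 0.003. If the larger share were in Europeans, the HR would fall below 1.

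**Step 3: equal shares.** A true HR of 1.00 stays at 1.00. Over one year, a true HR of 0.90 moves to 0.904, 0.911 and 0.920 at shares of 2%, 5% and 10%.

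**Step 4: first-line choice.** The spurious difference is Δf × (0.73 − m), where 73% is the plan's first-line metformin share and m is the metformin share among joiners (assumed). The gap in joiner share needed to produce the plan's detectable 1.4 points is 0.014 / (0.73 − m). It is 3.3, 6.1 and 10.8 points for m = 30%, 50% and 60%.

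**Step 5: check the benchmark.** Table 1 gives a detectable HR of 1.03 for 10.5K vs 120.4K. Events = 130,900 × 0.42 = 54,978, and the sum of the normal quantiles for two-sided 5% and 90% power is 3.2415.

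- Equal allocation: exp(3.2415 / √(54,978 × 0.25)) = 1.028, which matches the table.
- Stated allocation: exp(3.2415 / √(54,978 × 0.0802 × 0.9198)) = 1.052.

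The fair yardstick is therefore about 1.05, not 1.03.

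**The case against.** - **Calendar dates are not the whole safeguard.** A reader might infer that they are, and that would be wrong. The 6-month drug rule and the diabetes algorithm are both patient-level. The algorithm's cited source deals with prevalent and incident diabetes by title, and its diagram is not available here. For diabetes the gap may be partly closed. For hypertension, raised blood pressure and risk scores nothing equivalent is stated.
- **The rule may presuppose records.** The 6-month wording could be read as assuming that such records exist. The text does not say so, and an analyst could follow it without imposing that.
- **The direction is not fixed.** Entry for diabetes is the diagnosis date. If a new practice enters the original date, one before 2006 triggers the exclusion and a later one lengthens the apparent time to first prescription. The documents do not say how such dates are entered. This stands, and it rules out a claim about sign.
- **No ethnic difference in joiners is shown.** A reader might infer that the plan will produce false ethnic differences. No section gives the share of treated joiners in any group, so only the possibility is supported.
- **Passing 1.03 proves little.** That benchmark is about 1.05 at the stated group sizes, and the plan says it will weigh effect sizes rather than p values. The 3% vs 5% case lies below or just at 1.05.
- **The new-registrant sensitivity analysis.** It covers anyone registering since 2006, including people diagnosed years after joining, and the plan admits these analyses may introduce bias. How far it concentrates the problem is unknown. It is still poorly placed to reveal it.

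**Conclusion.** The point holds as a defect in the entry rule. As written, the plan allows already-treated joiners to be counted as incident, most clearly in the hypertension and CVD-risk cohorts and possibly in the diabetes cohort. It leaves the 6-month and 12-month look-back windows unobserved for some people, which weakens treatment staging and the engagement covariate whether or not ethnicity is involved.

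Bias in the ethnic comparisons is conditional on the share of such joiners differing by group, and its size and direction are unknown. The range of roughly 1.02 to 1.12 for a true HR of 1.00 rests on three assumptions: the joiner shares, a constant hazard, and prompt first prescriptions in joiners. It shows that modest differences in share could matter. It does not estimate what this study will find. The change should be made before analysis.

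**What to change.** In section L, require at least 12 months of research-standard registration in the current practice before the first qualifying diabetes, hypertension, raised-BP or CVD-risk entry. Apply this to every cohort and every sensitivity analysis, including the one in registrants since 2006. State in sections N and O that the 6-month prescription window and the 12-month consultation window must lie wholly within that period. If such a rule was already intended, or is built into the diabetes algorithm, the text should say so.

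The cost is one eligibility line and no new data. Some recent registrants will be lost. The documents do not allow the number to be calculated, and these are people with better ethnicity recording. If recent registration differs by ethnicity, the exclusion will differ too, so report the number excluded by ethnic group in each cohort.
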